### Data Analysis

The primary purpose of this exploratory project is to test the feasibility of an LSC intervention and to provide estimates of the efficacy of the LSC intervention to inform a future RCT. We will enroll a total sample size of 50 participants and expect an estimated 15% dropout rate. This sample size follows guidelines for pilot studies and is appropriate for exploring feasibility [51]. Descriptive statistics will be used to report sample characteristics, feasibility markers, and measures. Statistical analyses will be conducted using Stata (version 18.5; StataCorp LLC). Repeated-measures ANOVA will be applied to test for overall differences in loneliness and apathy at baseline, 3 months, and 6 months. Secondary outcomes will be analyzed for differences in trends before and after the intervention and associations with changes in loneliness and apathy. We will test whether these measures mediate changes in loneliness and apathy from baseline using linear regression models.

We will use field notes and memos throughout the qualitative interview process to explore qualitative data. Data will be deductively analyzed using NVivo 15 software.

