**Methods:**

A prospective, single-arm, single-center, pilot study will be conducted to compare loneliness and apathy in 50 lonely individuals without dementia at baseline who receive a virtual group reminiscence therapy intervention. The intervention will be delivered weekly over 12 weeks. Loneliness will be assessed with the UCLA Loneliness Scale and apathy will be assessed with the Apathy Evaluation Scale before and after the intervention. Feasibility will be assessed using quantitative and qualitative measures including feasibility of screening and enrollment, acceptability, and program satisfaction. Qualitative interviews will be conducted with a subset of 30 individuals to explore acceptability, barriers, and facilitators of the intervention.

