#### Intervention

LSC is a virtual, social storytelling space for older adults aged 60 and older where members can share life stories and connect with other members to promote a sense of belonging, purpose, and meaning. Clubs include up to 15 members that meet once a week for 1 hour. The number of participants per group is determined based on past levels of participation where 10-15 individuals are recruited per group and 6-8 attend each session due to the nature of the population (eg, multimorbidity and acute illness). The protocol for the study will not deviate from routine LSC protocols and will be offered similarly to the usual schedule and prompts as described in the introduction except for dedicated recording sessions which will be replaced by a usual session (Table 1). Clubs are led by a nonclinician facilitator who offers prompts to trigger discussion and reminiscence. Sessions begin with greetings after which 2 prompts are offered by the facilitator. The facilitator manages the group to encourage participation by all members. To promote technology equity (colloquially referred to as “techquity”), LSC has been delivered via live video or telephone according to participant preference to promote technology inclusiveness. Participants for this study will have the option to use video or telephone based on preference. The primary endpoint for this study will be 3 months based on durations of other RT interventions [31,34]. We will additionally collect assessment data at 6 months to preliminarily determine the feasibility and efficacy of a 6-month intervention in participants who continue to participate in the intervention over a longer period. Fidelity will be assessed via periods of observation by research staff to observe if components of the intervention are met (eg, 2 prompts per session and individual participation).

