### Data Collection

Assessments will be collected via telephone at baseline, 3 months, and 6 months post RT. Participants will receive a gift card for each completed assessment. Qualitative interviews will be conducted with a subset of 30 participants to assess satisfaction with the intervention, what aspects can be improved, and explore barriers and facilitators of participation, including digital literacy. A semistructured interview guide is included in Multimedia Appendix 1. Interviews will take place at an agreed-upon location over 60 minutes and will be conducted by the primary investigator or coinvestigator. We will collect data on the following outcome measures and covariates:

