### Primary Outcome

Our primary outcomes will be loneliness and apathy. This is based on our hypothesis that targeting these cognitive decline and dementia risk factors will result in improved cognition in the longer term. Given this is a feasibility study and 3- and 6-month intervals may be too short of a time frame to see a difference in cognition and that the study will not be powered to detect differences in cognition, we propose to examine differences in loneliness and apathy, risk factors for cognitive decline, which can plausibly change in this short interval.

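### The only analysis named for loneliness and apathy is an overall three-visit test, which does not isolate the declared 3-month primary endpoint or give the promised efficacy estimate

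*Protocol article*

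**What the plan says.** The Intervention section sets the time point: "The primary endpoint for this study will be 3 months based on durations of other RT interventions". The same section introduces the 6-month assessment as an addition, meant to look at feasibility and "efficacy of a 6-month intervention in participants who continue to participate in the intervention over a longer period". The abstract's Methods paragraph gives the programme length ("The intervention will be delivered weekly over 12 weeks"), so a 3-month visit falls at the end of the course.

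Under Primary Outcome: "Our primary outcomes will be loneliness and apathy". For these two outcomes the Data Analysis section names a single inferential method: "Repeated-measures ANOVA will be applied to test for overall differences in loneliness and apathy at baseline, 3 months, and 6 months". It names no contrast, mean change or interval at 3 months, although the section's stated purpose includes "to provide estimates of the efficacy of the LSC intervention to inform a future RCT".

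The Data Collection section lists the visits without limiting the last one to people who carry on: "Assessments will be collected via telephone at baseline, 3 months, and 6 months post RT".

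**The concern.** The declared question is whether loneliness and apathy change between baseline and 3 months. The declared test asks something else: whether the three visit means differ in any way. It has two degrees of freedom, no direction and no time point. A significant result could come wholly from month 6, and the result gives no figure to carry into the next trial's sample size.

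A second issue depends on details the article leaves open. The 6-month data are described with reference to people who continue. If 6-month assessment were limited to them, and the ANOVA needed all three visits, the primary comparison would rest on a subset that may have improved more than the rest. A single-arm study has no comparator to reveal that.

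**Working it through.** **Inputs from the article.** 50 enrolled and 15% dropout (Data Analysis); visits at baseline, 3 and 6 months; primary endpoint at 3 months. The sample size follows a pilot-study guideline, with no alpha, power, effect size or SD, so there is no power figure to reproduce. Retained: 50 × 0.85 = 42.5, taken as 42.

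**Assumptions, not in the article.** SD 1 at each visit, equal within-person correlation r = 0.7 (0.5 as a check), two-sided alpha 0.05, change of 0.3 SD.

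**Step 1: can the omnibus test tell month 3 from month 6?** The noncentrality is λ = n × Σ(μj − μ̄)² / (σ²(1 − r)), with 2 and 2(n − 1) = 82 degrees of freedom and critical F = 3.11.

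| True means (baseline, 3 m, 6 m) | Σ(μj − μ̄)² | λ = 42 × Σ / 0.3 | Omnibus power |
|---|---|---|---|
| 0, 0, −0.3 (month 6 only) | 0.01 + 0.01 + 0.04 = 0.06 | 8.4 | 72% |
| 0, −0.3, 0 (month 3 only) | 0.06 | 8.4 | 72% |
| 0, −0.3, −0.3 (both) | 0.06 | 8.4 | 72% |

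The three noncentralities are identical, so the F test rejects equally often whether the primary endpoint shows a change or not. In the first row a paired 3-month contrast would reject at its nominal 5%. With r = 0.5, λ = 42 × 0.06 / 0.5 = 5.04 and all three rows give 49%. The level moves with r, but the equality does not. No missing-data assumption is involved.

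**Step 2: does the omnibus test have less power?** For the 3-month contrast, the SD of change is √(2 × 0.3) = 0.775, the standardised change is 0.3 / 0.775 = 0.387, and the noncentrality is 0.387 × √42 = 2.51, which gives 69%. At equal n, with a sustained fall, omnibus against contrast is 72% v 69% (n = 42), 56% v 54% (n = 30) and 48% v 46% (n = 25). The problem is therefore not loss of power.

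**Step 3: what would a complete-case or continuers-only analysis do?** Suppose 60–70% of those retained continue (assumed): 42.5 × 0.6 = 25.5 and 42.5 × 0.7 = 29.8, so about 25–30 people have all three visits. Suppose also that continuing correlates 0.3 with improvement (assumed). The bias in the 3-month change is then 0.3 × φ(z)/q SDs of change:
- q = 0.6: 0.3 × 0.386 / 0.6 = 0.19, or 0.19 × 0.775 = 0.15 SD of the score.
- q = 0.7: 0.3 × 0.348 / 0.7 = 0.15, or 0.15 × 0.775 = 0.12 SD of the score.

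Simulated under these assumptions with no true change, the complete-case omnibus test rejected about 10–13% of the time. With stronger assumed selection (log-odds of 1 per SD of change) and 50–80% continuing, it rejected 18–39% of the time. When the ANOVA instead kept partial records in long format, a simulation of the 0.3-correlation case showed no bias (0.00 SD) and 5% rejection.

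**Step 4: what would the direct estimate deliver?** With 42 people assessed at 3 months, the 95% CI half-width is t(0.975, 41)/√42 = 2.02/6.48 = 0.31 SD of change.

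**The case against.** A baseline-to-3-month contrast is an ordinary follow-up to repeated-measures ANOVA, and an unseen analysis plan may name one. The abstract already speaks of measuring before and after the intervention, descriptive statistics are promised, and the study is exploratory with no alpha, power target or success rule. All of that stands and lowers the weight of the point. It does not remove it, because the article does state an analysis for its primary outcomes, and that analysis does not match its own endpoint.

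Three stronger readings are tempting, and the text does not support them.

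- **The ANOVA throws away 3-month data.** The article states no complete-case rule, and a long-format ANOVA in Stata can retain people who miss a visit.
- **The omnibus test is underpowered.** At equal n it is marginally more powerful than the contrast (Step 2). A gap such as 48% against 69% appears only when 25 completers are set against 42 people assessed at 3 months.
- **Month 6 is measured only in self-selected continuers.** The Intervention section gives a purpose for those data that concerns people who continue. Data Collection lists the 6-month call, with a gift card for each assessment, without that limit, and the T-MoCA footnote to Table 2 schedules a 6-month version without it too. The 15% dropout has no time point and may cover the whole study.

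The 'post RT' phrase could be read as counting months from the end of the course. Given a 12-week programme and an endpoint chosen from intervention durations, end-of-programme is the more natural reading of 3 months. This is loose wording to reconcile, not a demonstrated contradiction.

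**Conclusion.** The mismatch is real: the endpoint is at 3 months, but the named test pools 3 and 6 months and yields no estimate. Under the assumptions in Step 1 it is significant about 72% of the time for a 0.3 SD change confined to month 6, exactly as for one confined to month 3. That equality holds at any common correlation and equal SDs.

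Selection bias and loss of 3-month data are possible, not established. They need a complete-case rule or a continuers-only 6-month assessment, plus a continuation rate and a selection strength that the article does not give. The figures in Step 3 only illustrate this.

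Because nothing confirmatory rests on the test, the consequence is a mixed or missing planning estimate for the later trial. The point should be fixed but does not invalidate the study.

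**What to change.** - In Data Analysis, name the baseline-to-3-month mean change with 95% CI, for loneliness and for apathy, as the main estimate. Take it from a linear mixed model with visit as a categorical factor and all available assessments.
- Report the baseline-to-6-month contrast separately as secondary.
- State that all enrolled participants are assessed at 6 months whether or not they continue, and record continued attendance. Do not present results in continuers as efficacy of a 6-month intervention.
- Reconcile the 'post RT' wording in Data Collection with the 3-month endpoint in Intervention by stating the origin from which months are counted.

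Cost: a few sentences and one model command in Stata, plus possibly a few more 6-month calls and gift cards if non-continuers were not already to be contacted. Who is called at 6 months should be settled before follow-up begins, because assessments not made then cannot be recovered.

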### Secondary Outcomes

Secondary outcomes will be examined as potential mediators of effects between RT, loneliness, and apathy.

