The study has potential limitations. As a pilot study, the primary purpose of the proposed study is to test the feasibility of vGRT and provide preliminary efficacy data to improve loneliness and apathy. The pilot will include a single-arm and participants will not be randomized. The study will lay the groundwork for a future RCT of a LSC intervention to improve cognition in older adults. LSC engagement to date is consistent with prior work that has shown older adults can be exceptionally adherent to technological interventions with thoughtful planning and troubleshooting [52]. It is possible that technology access varies across populations and may affect the recruitment of diverse participants. We plan to collect quantitative and qualitative data regarding technology access which will inform future studies of LSC interventions. Future studies might also explore the provision of technology (eg, a tablet to allow access to videoconferencing software) to further promote access and participation. Currently, LSC is limited to 4 languages (English, Spanish, Cantonese, and Mandarin), which may exclude participants who speak other languages. In addition, the current study is restricted to individuals with and those without cognitive impairment and excludes individuals with dementia based on the AD8 assessment. The feasibility of LSC in its current format of virtual delivery, in a medium-sized group setting, with a nonclinical facilitator in individuals with advanced dementia remains an area of opportunity for future research.

In summary, this study will provide valuable data for a future RCT of a vGRT intervention to improve loneliness and apathy in community-dwelling older adults. If successful, the intervention can be widely scaled as a nonpharmacological intervention to prevent cognitive decline and promote social engagement in aging. The proposed methods to leverage community-based partnerships to establish and deliver effective interventions within communities can serve as a model for more community-engaged aging research.

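### Mediation of a reminiscence therapy effect cannot be tested by regression in a single arm; the analysis should be reported as association between changes

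*Protocol article*

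**What the plan says.** The Secondary Outcomes section of the protocol article gives these measures one role: "Secondary outcomes will be examined as potential mediators of effects between RT, loneliness, and apathy". The Data Analysis section turns this into a test: "We will test whether these measures mediate changes in loneliness and apathy from baseline using linear regression models". The sentence just before it already plans to relate the secondary outcomes to changes in loneliness and apathy, so the mediation test is an additional step.

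On design, the abstract says "A prospective, single-arm, single-center, pilot study will be conducted" and the Discussion says "The pilot will include a single-arm and participants will not be randomized". No comparator, attendance measure or other dose variable is named as the exposure for the mediation analysis. Under Data Collection, assessments are by telephone at baseline, 3 months and 6 months, with no separate schedule for mediators and outcomes.

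Cognition, measured by T-MoCA, is the first measure listed under Secondary Outcomes and so falls under the mediator sentence. The Primary Outcome section justifies loneliness and apathy as outcomes by the hypothesis that "targeting these cognitive decline and dementia risk factors will result in improved cognition in the longer term".

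**The concern.** To say that a measure mediates the effect of RT is to say two things: RT changed the measure, and that change altered loneliness or apathy. The first needs a contrast between receiving RT and not receiving it, and a study in which everyone receives RT has none. What remains is a regression of one change score on another. Such a slope can arise from a shared cause, such as a general shift in mood or health, the season, or a common way of answering two questionnaires, even if RT does nothing.

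The role given to cognition adds a conflict of direction. One section has cognition carrying the effect to loneliness and apathy; another has loneliness and apathy carrying the effect to cognition.

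At stake is a conclusion about mechanism that the design cannot support, in a study meant to provide preliminary data for a randomized trial.

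**Working it through.** **The plan's own figure.** The Data Analysis section says "We will enroll a total sample size of 50 participants and expect an estimated 15% dropout rate". The size rests on pilot-study guidance, with no alpha, power, effect size or SD stated, so 50 cannot be re-derived. The dropout arithmetic is 50 × (1 − 0.15) = 42.5, so about 42 completers.

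**What one arm can estimate.** Let ΔM be the change in a secondary measure, ΔY the change in loneliness or apathy, and A the indicator of receiving RT.

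- Mediator model: ΔM = a0 + a1·A + error
- Outcome model: ΔY = b0 + b1·A + b2·ΔM + error
- Indirect effect of RT: a1 × b2

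With A = 1 for everyone, the column for A is identical to the intercept. At n = 42 the matrix [1, A, ΔM] has rank 2 of 3; with two arms of 21 it has rank 3 of 3. In one arm the mediator model yields only the sum a0 + a1, the mean change. Separating a1 requires setting a0 = 0, that is, assuming no change without RT. In the outcome model only b2, the slope of change on change, can be estimated, and it carries a causal meaning only if no unmeasured factor moves both measures.

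**How often the slope is significant with no RT effect.** Let ρ be the correlation of the two change scores for reasons unrelated to RT. The document gives no value, so 0.3 to 0.5 is an assumed range. With n = 42 and a two-sided 5% test, the Fisher z approximation gives z = atanh(ρ) × √(n − 3) = atanh(ρ) × √39, and the probability of p < 0.05 is about Φ(z − 1.96).

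| ρ (assumed) | z | Probability of p < 0.05 |
|---|---|---|
| 0.3 | 1.93 | 49% |
| 0.4 | 2.65 | 75% |
| 0.5 | 3.43 | 93% |

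A simulation with 10,000 runs per setting, in which RT affected neither measure and the mediator did not affect the outcome, agreed: about 5% at ρ = 0, 49–50% at 0.3 and 93–94% at 0.5.

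**Using time as the exposure.** A pre-post mediation model can be fitted by letting time stand for RT and requiring both a significant mean change in the mediator and a significant slope. In the same simulation, with a common drift d (in SD units of change, assumed) unrelated to RT, both tests were significant this often:

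| d (assumed) | ρ = 0.3 | ρ = 0.5 | ρ = 0.7 |
|---|---|---|---|
| 0 | 2% | 5% | 5% |
| 0.3 | 23% | 45% | 47% |
| 0.5 | 44% | 83% | 89% |

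False mediation stayed at or below about 5% only with no drift or no correlation. With 21 + 21 randomized participants, the corresponding joint test gave 0.2% to 5.2% over all settings. Randomization protects only the RT-to-mediator path; unmeasured common causes of mediator and outcome would remain.

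**Direction of cognition.** Secondary Outcomes gives RT → cognition → loneliness and apathy. Primary Outcome gives RT → loneliness and apathy → cognition, and adds that 3 and 6 months may be too short to see a difference in cognition. A measure not expected to move within the study is a poor candidate to explain change within it.

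**The case against.** The best defence is that this is one sentence about a secondary analysis in a project described as exploratory, whose only stated hypothesis concerns feasibility and acceptability. The sample size, feasibility benchmarks and primary comparison do not depend on it, and the mediators are called potential. This stands, and it limits the severity. It does not rescue the test: exploratory status excuses imprecision, not the absence of a contrast.

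A reader might infer that no mediation model can be fitted or that the data have no time order. The document does not support that. A pre-post model is possible, and three assessments allow a lagged model from 3 to 6 months. Attendance and continuation to 6 months also vary. But these routes rest on untestable assumptions or on self-selected exposure, and the article adopts none of them. A fuller analysis plan could specify the model; it could not add the missing comparison.

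The percentages are, strictly, power to detect a real correlation. They become false-positive rates for mediation only if a significant slope is given that label.

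It is also tempting to multiply six measures in Table 2 by two outcomes and count 12 such tests. The illustration concerns two self-report scales. It does not carry over to T-MoCA, a scored test, or to diagnosed conditions, for which a 3-month change score means little. The Secondary Outcomes text describes only four instruments.

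Finally, a reader might infer that the results will be published as mechanism or used to choose the targets of the later trial. No section says so. The Discussion acknowledges the single arm as a limitation but draws no consequence for mediation.

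On cognition, the Primary Outcome section speaks of the longer term and the mediator sentence is loosely worded. The two still need to be reconciled.

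**Conclusion.** The concern holds in a limited form. As written, the plan tests mediation of an RT effect in a design that cannot separate such an effect from time, drift or regression to the mean, except by assuming no change without RT. The regression can show association between changes and no more. With about 42 completers and assumed RT-unrelated correlations of 0.3, 0.4 or 0.5 between two self-report change scores, it is significant in about 49%, 75% or 93% of studies. The rank result follows from the design alone; the percentages depend on the assumed correlations. The conflicting position of cognition is a real but smaller inconsistency.

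Severity is moderate. The analysis is secondary and exploratory, and the feasibility aims are unaffected.

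**What to change.** - Delete the mediation test from Data Analysis and the word mediators from Secondary Outcomes.
- Report the associations between change scores that are already planned, with 95% confidence intervals, as descriptive and hypothesis-generating.
- Treat T-MoCA as an outcome only, which removes the conflict with the Primary Outcome section.
- State that mediation is left to the randomized trial.

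The cost is wording and the loss of one exploratory claim about mechanism. The same data are collected and no planned association is lost.

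A separate minor point can be settled in the same edit: Table 2 lists the FRAIL Scale and diagnosed conditions as secondary outcomes, while the Covariates section uses them to describe the population. The two should be reconciled.

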**Figure 1 figure1:**
[figure not shown]
Conceptual model of a reminiscence therapy intervention for loneliness and apathy and mechanisms for how the intervention may work. The left side of the figure represents the current proposal where we propose to investigate the feasibility of reminiscence therapy for loneliness and apathy. This research will inform and support a future randomized controlled trial of a reminiscence therapy intervention to improve cognition.

Cognitive decline in aging is multifactorial with multiple possible causes and there is significant variability in cognition based on the presence or absence of risk factors such as social factors (eg, loneliness) and apathy. In addition, the multiple aspects of social relationships (eg, meaning and purpose in life and social support) and psychological well-being (eg, depression) influence cognition via multiple possible paths. Meaning and purpose in life were associated with cognitive decline, and incident MCI and Alzheimer disease in prior studies [25]. In addition, studies investigating volunteering interventions to provide meaningful social, physical, and cognitive activities for older adults reduced brain aging [26]. RT is similarly organized to provide structured social engagement and stimulate cognitive activity through exercising autobiographical memory [27] and improvements in cognition may be mediated through improved life meaning and purpose. Depression is a well-known risk factor for cognitive decline [28] and loneliness and the relationship between loneliness and depression may be bidirectional [29]. In addition, apathy and depression are distinct neuropsychiatric conditions that often co-occur and symptoms may overlap [30]. Given the mechanisms of RT are not well understood, multiple aspects of social relationships and psychological well-being may be considered as mediators of the relationship between RT and health outcomes.

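### In a single-arm study where everyone receives reminiscence therapy, the planned regression can show that changes are associated but cannot test mediation of the therapy's effect

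*Protocol article*

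**What the plan says.** The Secondary Outcomes section sets the aim: "Secondary outcomes will be examined as potential mediators of effects between RT, loneliness, and apathy". The Data Analysis section sets the method: "We will test whether these measures mediate changes in loneliness and apathy from baseline using linear regression models". The sentence before that one already plans to look at before-after trends in the secondary outcomes and at how they relate to change in the two primary outcomes.

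The design is stated in the abstract ("A prospective, single-arm, single-center, pilot study will be conducted to compare loneliness and apathy in 50 lonely individuals without dementia at baseline") and again among the limitations in the Discussion: "The pilot will include a single-arm and participants will not be randomized". On timing, Data Collection says: "Assessments will be collected via telephone at baseline, 3 months, and 6 months post RT". No comparison group, dose variable or lag is named for the mediation analysis. On direction, the Background text after Figure 1 says that "the relationship between loneliness and depression may be bidirectional".

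**The concern.** Mediation of a therapy effect has two links: the therapy changes the mediator, and the mediator changes the outcome. The first link needs a contrast between receiving the therapy and not receiving it, and this study has none. Time can stand in for the contrast, but then natural change, regression to the mean and repeated assessment are all counted as therapy.

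The second link is estimated from scales taken at the same calls. Mood and social scales can move together for many reasons, and the article itself allows that loneliness may drive depression as well as the reverse.

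What is at stake is the wording of a conclusion. A pilot meant to prepare a randomised trial could report how RT works from data that would look the same if RT did nothing.

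**Working it through.** **Inputs from the article.** One arm, no randomisation. Size: "We will enroll a total sample size of 50 participants and expect an estimated 15% dropout rate". Expected completers: 50 × (1 − 0.15) = 42.5, taken as n = 42. The 50 cannot be reproduced by a power formula, because its stated basis is only that "This sample size follows guidelines for pilot studies and is appropriate for exploring feasibility". No figure is given for the mediation analysis.

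**Assumed, because the article does not give them.** Two-sided 5% level per test; correlation r between change in mediator and change in outcome; drift d, the mean change in the mediator without therapy, in SDs of the change score.

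**Step 1: what can be estimated.** Let T be therapy, M change in the mediator and Y change in the outcome.

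- M = a0 + a·T + error
- Y = b0 + c·T + b·M + error
- Mediated effect = a·b

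Here T = 1 for everyone, so the T column equals the intercept column and the matrix [1, T, M] has rank 2, not 3. Neither a nor c is estimable. Only the sum a0 + a can be estimated, which is background change plus therapy effect in one number. No sample size alters this.

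**Step 2: direction.** If the model is a simple regression of Y on M, the test is t = r·√((n − 2)/(1 − r²)). It depends on the data only through r, and r is the same with M and Y exchanged. In a simulated data set of 42, both directions gave p = 5.99 × 10⁻⁵. This exact symmetry belongs to the simple model only.

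**Step 3: illustration with no RT effect, n = 42.**

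Slope alone (40,000 simulated studies per value):

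| r | slope significant |
|---|---|
| 0 | 5.1% |
| 0.2 | 25.2% |
| 0.3 | 49.7% |
| 0.4 | 76.6% |
| 0.5 | 93.5% |

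Slope and mean change in the mediator both significant (20,000 per value):

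| drift d | r = 0.3 | r = 0.5 |
|---|---|---|
| 0 | 2.1% | 4.4% |
| 0.2 SD | 11.1% | 22.9% |
| 0.3 SD | 22.7% | 43.8% |
| 0.5 SD | 44.2% | 82.4% |

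The first table gives the power to detect a correlation that is really there. It counts as an error only when that correlation is called mediation of an RT effect. The second shows that requiring a mean change controls the error when nothing drifts, and that the control is lost as drift grows. One arm cannot show how large the drift is.

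**The case against.** The strongest reply is that this is an exploratory secondary analysis in a feasibility study. The measures are called only potential mediators, the single arm is disclosed, and no feasibility benchmark, primary analysis or sample size depends on the sentence. That stands, and it limits the severity. The disclosed limitation is not tied to the mediation test, however.

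A second reply is that details belong in an analysis plan. That holds for model form, but no analysis plan can supply an untreated group.

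A third is that a before-after look at the secondary outcomes is already planned and could serve as the first link. This partly stands: it brings the illustrative rate down to 2% to 4% if nothing drifts. The article does not make it a condition of the mediation test, and the no-drift assumption cannot be checked here.

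A fourth is that the amount of therapy varies with attendance, and that three time points permit a lag. Neither analysis is stated. The Intervention section links low attendance to multimorbidity and acute illness, so attendance would be a confounded dose. A lag would give time order but still no untreated contrast.

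A reader might infer several stronger points that the documents do not support:

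- That the planned test has a 50% to 94% false-positive rate. The model is given only as linear regression, and the correlations are assumed.
- That mediator and outcome are interchangeable in any version of the model. This is shown only for the simple change-on-change form.
- That multiplicity is a further error. The number of tests is not stated, and its handling is commonly left to an analysis plan.
- That mediation results will shape the randomised trial. The article says that efficacy estimates will inform it and does not say this of mediation.

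**Conclusion.** The point holds as a matter of identification: the design has no contrast from which an effect of RT on a mediator could be estimated, so mediation cannot be tested as planned. This does not depend on any assumed number. With simultaneous measurement and no stated lag, the regression also cannot establish direction.

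The size of the risk is conditional. It runs from a few per cent to a large majority of studies, depending on the correlation between change scores, on whether a mean change is required, and on drift without therapy. None of these is given in the article.

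This should be fixed before analysis, but it is not a critical fault. It restricts what may be concluded about mechanism and leaves the feasibility objective as it was.

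**What to change.** In Data Analysis, delete the mediation sentence. Report the associations already planned between changes in the secondary outcomes and changes in loneliness and apathy as estimates with 95% confidence intervals, and state that mediation is neither tested nor claimed.

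In Secondary Outcomes, replace the mediator sentence with: *Secondary outcomes are candidate mediators for the future RCT and are described here as correlates of change in loneliness and apathy.* The list of measures need not be shortened.

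If a lagged look is wanted (change to 3 months in a candidate against the 6-month outcome), label it as association. Note beside it that the Intervention section intends the 6-month data for participants who carry on with the clubs, which may be a smaller and selected group.

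The cost is wording in two places, with no new data and no change in sample size. The downside is that this pilot makes no claim about mechanism, which is left to the randomised trial.
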